**Methods/design:**

LIPLEG is a randomised controlled multicentre investigator-blinded trial. Women with lipedema (*n*=405) without previous liposuction will be allocated 2:1 to liposuction or CDT. The primary outcome of the trial is leg pain reduction by ≥2 points on a visual analogue scale ranging 0–10 at 12 months on CDT or post-completion of liposuction. Secondary outcomes include changes in leg pain severity, health-related quality of life, depression tendency, haematoma tendency, prevalence of oedema, modification physical therapy scope, body fat percentage, leg circumference and movement restriction.

The primary analysis bases on intention-to-treat. Success proportions are compared using the Mantel-Haenszel test stratified by lipedema stage at a 5% two-sided significance level. If this test is statistically significant, the equality of the response proportions in the separate strata is evaluated by Fisher’s exact test in a hierarchical test strategy.

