Liposuction is therefore discussed as a useful addition to or even alternative therapy for CDT, especially in the early stages of lipedema in order to prevent possible long-term effects such as the development of secondary lymphedema and disease progression, to improve the quality of life and to reduce the need for CDT [4, 11, 20–22].

In summary, clinical experiences as well as small trials demonstrate a positive effect of liposuction in lipedema with respect to pain, movement improvement and quality of life. However, controlled and randomised clinical trials comparing conservative and surgical treatments with valid statistical methods are missing. There is no evidence that surgical treatment is equivalent or even superior to conservative treatment with respect to pain in lipedema stages I, II and III. Therefore, a large-scale randomised controlled investigator-blinded trial will be performed with the aim to provide a definitive answer.

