### Sample size

#### Determination of trial size

According to the results of Schmeller et al. [22, 23], the success proportion of the intervention at each stage is expected to be at least 40% and that of the control to be at most 10%. The chi-square test requires 111 patients (74 vs. 37) per group to reach 80% power at two-sided significance level of 5% to detect such a difference. To compensate for the influence of dropouts and stratification, 135 patients per stage are included (this corresponds to an increase of approx. 20%). Accounting for up to 10% attrition from baseline to follow-up, the number of 450 patients is required in total.

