### Statistical methods

The primary analysis is according to the intention-to-treat. The primary outcome ‘success’ is evaluated by the stratified (by stage) Mantel-Haenszel test [25] at two-sided significance level of 5% (H_0_: odds ratio = 1 vs. H_A_: odds ratio ≠ 1). If this test is statistically significant, the equality of the success rates in the separate stages is evaluated by Fisher’s exact test (hierarchical test strategy). A missing primary outcome or change of the randomly assigned treatment is counted as failure. No interim analysis is planned. Secondary is the analysis of patients treated and observed per protocol (i.e. completed liposuction or ≥80% of planned CDT sessions done; valid primary outcome). Secondary and further outcomes are evaluated without adjusting for multiple hypothesis testing (i.e. no alpha correction is applied). Distributions of quantitative variables are described as mean (standard deviation) and percentiles (0, 25, 50, 75, 100), qualitative variables are summarised by count and percentage. The impact of missing outcome data is assessed by sensitivity analyses based on single/multiple imputation. The information on AEs is assessed (according to severity, intensity of symptoms, causal relationship to the CDT or intervention), coded and summarised by contingency tables. Subgroup analysis is done by patient age, study centre and surgeon.

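### The stage-specific Fisher tests that follow the overall test have no stated order, alpha split or level, and the overall test alone gives only weak family-wise control over them

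*Protocol article*

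**What the plan says.** The primary analysis is the "stratified (by stage) Mantel-Haenszel test [25] at two-sided significance level of 5" per cent (Protocol article, Statistical methods). The same section continues: "If this test is statistically significant, the equality of the success rates in the separate stages is evaluated by Fisher’s exact test", and labels the strategy hierarchical. The abstract (Methods/design) says the same of the strata: each comparison "is evaluated by Fisher’s exact test in a hierarchical test strategy". Neither place names an order of stages, a division of alpha or a significance level for the Fisher tests. The 5% is attached to the overall test.

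The only hint of a level per stage is in Determination of trial size. There "the success proportion of the intervention at each stage is expected to be at least 40" per cent and "that of the control to be at most 10" per cent, the test is two-sided at 5%, and 135 patients are planned for each stage. The statement in Statistical methods that no alpha correction is made is limited to secondary and further outcomes, so it does not cover the stage tests of the primary outcome.

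**The concern.** An overall test placed in front of three subgroup tests controls the chance of a false stage claim if all three stages are null, because the overall test then opens the way only about 5% of the time. If one stage benefits strongly, that stage opens the gate almost by itself. The other two are then tested side by side with no further protection unless an order or an adjustment is specified.

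This matters because stage conclusions appear to be intended. The Background notes the lack of evidence "with respect to pain in lipedema stages I, II and III", and the sample size is built up stage by stage. At stake is a claim that liposuction works in a stage where it does not, under a label that leads the reader to expect error control.

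**Working it through.** **Inputs from the article.** Three stages; 135 patients per stage; 2:1 allocation, hence 90 vs 45; 40% vs 10% success; overall Mantel-Haenszel test at two-sided 5%; Fisher's exact test per stage.

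**Assumptions.** Fisher at 5% in each stage (inferred from the sizing); equal stage sizes; success rates of 10% to 50% in null stages; effects above 40% vs 10%; no continuity correction in the Mantel-Haenszel test.

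**The plan's own figure.** For 80% power at 10% vs 40%, 2:1, two-sided 5%, the pooled rate is (0.10 + 2 × 0.40)/3 = 0.30. The control group needs [1.96 × √(1.5 × 0.30 × 0.70) + 0.842 × √(0.10 × 0.90 + 0.40 × 0.60/2)]² / 0.30² = 24.5, so 25 + 50 = 75 patients, or 90 with continuity correction. The stated 111 (74 vs 37) is not reproduced at 80% power; it results from 90% power with continuity correction. This is a separate matter. The steps below use 90 vs 45.

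**Step 1: nominal bound.** With two null stages, an open gate and 5% each: 1 − 0.95² = 9.75%.

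**Step 2: actual size of Fisher's test at 90 vs 45**, by exact enumeration, and the result s for two null stages with the gate certain to open, 1 − (1 − s)²:

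| Success rate in null stages | Size s | Two null stages |
|---|---|---|
| 10% | 3.3% | 6.6% |
| 20% | 3.8% | 7.4% |
| 30% | 3.9% | 7.7% |
| 40% | 4.05% | 7.9% |
| 50% | 4.4% | 8.7% |

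**Step 3: include the gate.** The gate opens when [Σ(X − E)]² / ΣV > 3.84, summed over stages. X is the number of liposuction successes, m the total successes in the stage, E = 90m/135 and V = m(135 − m) × 90 × 45/(135² × 134). With 400,000 simulated trials per scenario:

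| True pattern | Family-wise error |
|---|---|
| All three stages null | 2.3-2.8% |
| One stage 40% vs 10%, two null at 10-40% | 3.5-4.0% |
| One stage 50% vs 10%, two null | 4.5-5.1% |
| One stage 60% vs 10%, two null at 10% or 30% | 6.2%, 5.9% |
| One stage 70% vs 10%, two null at 10-50% | 6.5-7.6% |
| Two stages 40% vs 10%, one null at 40% | 3.6% |

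The gate opens in 51% to 77% of trials in the second row and in about 98% or more in the fifth, which explains the difference. With a single null stage the error cannot exceed that stage's own test size, at most 4.4% by step 2.

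**Step 4: candidate remedies.** At 40% vs 10% in all stages, power is:

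| Rule after the overall test | Per stage | All three stages |
|---|---|---|
| 5% each | 97.4% | 92.4% |
| Holm | 97.1% | 92.2% |
| Closed testing | 97.4% | 92.4% |

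If only one stage works (40% vs 10%), its power is 77.1% unadjusted, 75.5% with Holm and about 74.3% with closed testing when the null rate is 10%. At a null rate of 30% the figures are about 54.6%, 53.6% and 49.0%. In the scenarios with two null stages, Holm holds the family-wise error at or below 3.3%.

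**The case against.** A reader might infer that the plan tests every stage at 5% and that its hierarchy is therefore one in name only. The article does not support this. It gives no level for the Fisher tests, and 5% per stage is an inference from the sizing. A fixed sequence of stages would deserve the name and would control the error. Such an order may stand in the full protocol (version 02_0) or in an analysis plan, neither of which is shown, and an article may well have condensed it away. That part of the objection stands, and it limits the point to what the printed text leaves open.

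A reader might also take 9.75%, or the 14.3% of three ungated tests (1 − 0.95³), as the true error. Neither applies. The gate holds the case of three null stages, and Fisher's test at these sizes stays below its nominal level.

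The primary objective is overall superiority, tested once at 5% with no interim analysis, so the main claim is protected. The excess needs exactly two null stages and an effect in the third well above 40% vs 10%. The plan expects at least 40% success with liposuction in every stage, so two null stages go against its own premise. All of this is correct and makes the point a small one. It does not remove it, because the article presents the stage tests as part of the primary testing strategy, and the description as printed does not secure the control that the label suggests.

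**Conclusion.** The concern holds in a limited form, and its severity is minor. As printed, the strategy is one gate followed by three stage tests with no order, split or level, and a gate alone controls the family-wise error only when all stages are null. Under the reading of 5% per stage, the error is about 6 to 7.5% with two null stages and an assumed 60-70% vs 10% in the third. It is about 3.5 to 4% when that stage has the design effect of 40% vs 10%, and at most 5% when no more than one stage is null. These figures rest on 90 vs 45 analysed per stage and on assumed null-stage rates of 10% to 50%. The documents do not show that the full protocol lacks an order of stages. The overall test of liposuction against CDT is not in question.

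**What to change.** State in the analysis plan, before stage results are known, that if the overall Mantel-Haenszel test is significant, Holm's procedure is applied to the three Fisher p-values. The smallest is compared with 5%/3 = 1.67%, the next with 2.5% and the largest with 5%, stopping at the first that fails. This controls the family-wise error at 5% whatever the pattern of effects. If the full protocol already intends a fixed sequence of stages, each tested at 5% only after the one before it succeeds, naming that order is sufficient instead.

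No extra patients are needed. With Holm, the loss is 0.3 points of power per stage (97.4% to 97.1%) and 0.2 points for all three stages (92.4% to 92.2%) when every stage has 40% vs 10%. It is about 1 to 1.6 points for the effective stage when only one works. If two stages work, the weaker of their results is usually judged at 2.5%, where Fisher power is 94.5% instead of 97.4%, a loss of about 3 points.

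Closed testing with Mantel-Haenszel tests on pairs of stages is also valid. It loses nothing when all stages benefit equally but costs about 3 to 6 points when only one does, so it is not the preferred remedy.

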### Monitoring

The trial sites will be monitored closely to ensure patient’s safety and the quality of the data collected. Monitoring is performed risk-based. The CRA will review informed consent forms, verify the completeness and accuracy of the patient data collected and ensure that the trial is conducted in accordance with the protocol, ICH-GCP principles and legal requirements.

Each trial site received a site selection visit to ensure staff qualification and experience, and sufficient capacity and equipment. The initial training of each site was performed during an initiation visit prior to trial start. A total of 140 regular monitoring visits are planned. The frequency of the regular monitoring visits at the trial site depends on the recruitment rate and the quality of the documented data at the trial site. Each site will also receive a close-out visit, for formal termination of the trial at the respective trial site.

#### Data Monitoring Committee

A Data Monitoring Committee (DMC) oversees the safety of the patients in the trial by periodically assessing selected trial safety datasets and their influence on the risk-benefit assessment for patients and the justifiability of further trial conduct. The DMC receives a list of AEs and SAEs at regular intervals. As described in a separate DMC manual, the assessment of SAEs is based on the absolute rates, and the difference in rates and the temporal development of the SAEs that occurred. Based on this, the DMC will make recommendations on continuation, modifications or even termination of the trial to the sponsor. It consists of two physicians and a statistician, who are independent experts, not otherwise involved in the conduct of the trial, and operate based on an agreed charter.

#### Adverse events and safety reporting

All AEs and SAEs occurring during the trial will be documented in the patient’s medical records and the eCRF, including date and time of onset and resolution, severity, causal relationship with CDT/liposuction, seriousness and measures. In addition, SAEs are immediately sent to the principal coordinating investigator (PCI) via an automatic e-mail notification directly from the database. The risk-benefit ratio will be checked by the PCI based on a list of AEs that have occurred up to that point, which is made available at regular intervals by the CTCC. All safety-relevant events will be promptly reported to the Ethics Committees and the DMC.

#### Auditing

No auditing is planned during the trial. However, the sponsor has the right to carry out quality assurance audits at the trial site and other institutions that may be involved in the study, whenever deemed necessary. The aim of audits is to check the validity, verifiability and completeness of the data and the credibility of the clinical study as well as to check whether patients’ rights and safety are guaranteed. The sponsor can commission people who are otherwise not involved in the clinical trial (auditors). They are permitted to inspect all trial-related documents (in particular: trial protocol, questionnaires, patient files, trial-related correspondence).

The sponsor and all participating trial sites commit to support auditors and, in this context, to grant the authorised persons access to the original documents.

All auditors commit to treat personal and other data confidentially.

### Ethics and dissemination

The trial was approved by the following Ethics Committees: Ethics Committee of the Hesse State Chambers of Physicians (corresponding Ethics Committee; reference number Az. 2019-1377-evBO), Ethics Committee of the Medical Association of North Rhine (reference number: 2019316), the Ethics Committee of the Saxon State Chambers of Physicians (reference number: EK-BR-76/19-1), Ethics Committee of the Brandenburg State Chambers of Physicians (reference number: AS 117(bB)/2019), Medical Ethics Committee of the University of Oldenburg (reference number: 2020-009), and Ethics Committee of the Baden-Württemberg State Chambers of Physicians (reference number: B-F-2019-075). The ethics committee of the University of Regensburg and of Bavarian Medical Association does not require an additional ethics vote, after the study protocol has been approved by other German ethics boards. In case of important protocol modifications, the PCI will inform the PIs of all trial sites. They will then forward the amendments to the associated ethics committees and trial participants. Written informed consent is provided by all participants prior to any trial procedure. A patient insurance policy is taken out for all included patients. Address, insurance number, telephone and fax number of the insurance company are included in the informed consent. In addition, patients will be insured for travel to the way to the regarding trial site.

The trial is conducted in accordance with the International Conference on Harmonisation for Good Clinical Practice (ICH-GCP). The trial will always comply with the Declaration of Helsinki.

The results of this trial will be submitted for publication in peer-reviewed scientific journals and presented at national and international conferences.

## Discussion

Lipedema, first described by Allen and Hines in 1940 [1], is a disease of adipose tissue that appears almost exclusively in women, mostly at a time of hormonal change (e.g. puberty, pregnancy or menopause). It is believed to be a genetic disease, probably with an X-linked dominant inheritance, or autosomal dominant with sex limitations [3].

The phenotype is characterised by a typical bilateral disproportionate distribution of adipose tissue on the extremities. Main symptoms include a progressive symmetrical non-pitting, fatty swelling of the extremities, with recessing of the hands/feet, easy bruising, pain and lack of response to weight reducing diets [1].

Up to now, there are no curative therapies for lipedema. As an insufficiently managed lipedema will likely progress to lipo-lymphedema, the management of the disease is crucial and consists of two main goals: firstly, improvement of the subjective discomforts (e.g. pain) and secondly, the prevention of further complications (lipo-lymphedema, skin infections, psychological morbidities and mechanically caused complaints such as disorder of gait and joint deformities) [26].

Conservative treatment such as manual lymph drainage, multi-layered short stretch bandaging or medical compression stockings can ameliorate the pain of lipedema patients and prevent a concomitant edema formation [27]. A reduction of the pathological adipose tissue with conservative treatment is not possible [26].

Liposuction as a surgical intervention is an accepted therapeutic approach for the treatment of lipedema, especially when conservative therapies are insufficient or have failed [26, 28]. Liposuction is used for a reduction of the pathological subcutaneous fat tissue and aims to improve the mobility and subjective complaints by reducing the fat tissue volume of the affected extremity.

Up to now, conclusive long-term data are still missing, but short-term results seem promising, especially when the intervention is performed in an early stage of the disease in wet-technique with blunt cannulas [11, 22, 29].

The LIPLEG trial assesses whether surgical treatment of lipedema is safe and effective to reduce pain and other lipedema-related health problems.

Moreover, this study is the first randomised controlled and blinded study to compare conservative to surgical treatment. The findings of this trial will potentially influence standard of care in lipedema.

### Trial status

The authors confirm that the trial was registered prior to the submission of this manuscript (ClinicalTrials.gov Identifier: NCT04272827, registered on 14 February 2020). Recruitment of participants is expected in December 2020, last patient’s last visit is expected in summer 2025.

## Data Availability

Not applicable

## Abbreviations

AE: Adverse event
CDT: Comprehensive decongestive therapy
CQC: Central quality control
CRA: Clinical research associate
CTCC: Clinical Trials Centre Cologne
DLQI: Dermatology Life Quality Index
DMC: Data Monitoring Committee
EC: Ethics committee
eCRF: Electronic case report form
IMSB: Institute of Medical Statistics and Computational Biology
LEFS: Lower Extremity Functional Scale
PCI: Principal Coordinating Investigator
PHQ-9: Patient Health Questionnaire-9
PI: Principal Investigator
SAE: Serious adverse event
SF-36: Short Form 36
TA: Tumescent anaesthesia
WAL: Water-assisted liposuction
WHOQOL-BREF: World Health Organization Quality of Life-abbreviated version of the WHOQOL 10
